##### 4.1.1.1 Primary variables

The primary variables will be surface contour captured by the 3-dimensional 180° camera, lumpectomy dimensions captured by ultrasound, predicted surface contour and predicted lumpectomy dimensions from the multiscale model.

##### 4.1.1.2 Secondary variables

Secondary variables will be the assessment of pain over the course of the 6-month treatment and healing process, the assessment of pain associated with ultrasound (pre- ultrasound to post-ultrasound pain assessments per visit), surface temperature changes related to healing using a thermal imaging camera, and judgment of independent reviewers regarding the correlation of the cosmesis score to the multiscale prediction model.

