In our laboratory, we have performed 3-D virtual surgery using patient MRI data and studied the cosmetic impact of BCT operation. This simulation was restricted to the immediate impact of mechanical tissue removal and may predict the immediate contour result of surgery, not the final shape of the breast after healing and has not been compared to results in actual patients.

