### 1.1 Approach to the problem

The immediate impact of tissue removal on breast deformation, as a function of tumor location and size, has been defined by our work using 3-dimensional reconstruction of the breast shape from MRI data taken with patients in a prone position. This approach uses a mechanical model that combines a hyper-elastic model of the soft tissue and a mechanical model of the skin envelope to compute breast deformation as a function of the position of the patient in two consecutive steps: position of the breast at zero gravity and at various gravity loads. From this information, a Graphical User Interface (GUI) is being developed to allow the surgeon to remove tissue in a virtual environment and visualize (or predict) the outcome. Pressures inside the wound will also impact the outcome, so an additional GUI will be developed to simulate changes that occur during treatment (eg, radiation therapy) and healing. In order to confirm the predictive validity of the multiscale model of breast lumpectomy and healing, we plan to study patients who are actively undergoing the surgical removal of breast tissue, treatment for breast cancer, and breast tissue healing.

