## **2 Purpose and objectives**

### **2.1 Purpose**

The purpose of this study is to test the predictive validity of the multiscale model of breast lumpectomy and healing in patients undergoing BCT for breast cancer and identify targets for improvement in BCT.

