### 6.8.1 Sequence of events

| Month               |          |   | 1 |    |    |    | 3 | 6 |    |
|----------------------------|----------|---|----------|----|----|----|----------|----------|----|
| Week                |          |   | 1        | 3  | 6  | 10 | 12       | 24       | 26 |
| Visit day           | -21 to 0 |   | 1        | 2  | 3  |    | 4        | 5        |    |
| Visit window (days) | -21      |   | 0        | ±7 | ±7 |    | ±7       | ±7       |    |
| Visit number        | 1        |   | 2        | 3  | 4  |    | 5        | 6        |    |
| Parameter           |          |   |          |    |    |    |          |          |    |
| Informed consent           | X        |   |          |    |    |    |          |          |    |
| 3-D SI*                    | X        |   | X        |    | X  |    |          | X        |    |
| Surgery                    |          | X |          |    |    |    |          |          |    |
| Thermal image              |          |   | X        | X  | X  |    | X        | X        |    |
| Ultrasound†                |          |   | X        | X  | X  |    | X        | X        |    |
| Radiation therapy          |          |   | X        | X  | X  |    |          |          |    |
| Pain scale score‡          | X        |   | XX       | XX | XX |    | XX       | XX       |    |
| Cosmesis judging§          |          |   | X        |    |    | X  |          |          | X  |

\*3-dimensional 180° camera surface imaging

†Breast ultrasound of the tumor / lumpectomy area

‡Performed pre and post ultrasound

§Independent assessment of cosmesis using the Harvard/NSABP/RTOG cosmesis criteria and comparison to multiscale model

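### The protocol sets out to test a prediction but never requires it to be fixed before the outcome is seen; separately, a secondary cosmesis judgment is not blinded to the model

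*Protocol*

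**What the plan says.** **The purpose and the criterion.** Section 2.1 states that the study is to "test the predictive validity of the multiscale model of breast lumpectomy and healing in patients undergoing BCT". Section 4.1.1 makes agreement between the observed surgical and healing outcome and the model's predictions the primary endpoint, with a mean combined score of at least 60% as acceptable. Section 7.1.3 repeats the 60% as a mean accuracy rate for a combined score of three processes, assessed at weeks 10 and 26.

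**The state of the model.** On the sponsor's existing work, the Background says "This simulation was restricted to the immediate impact of mechanical tissue removal". It adds that the result may give the immediate contour, "not the final shape of the breast after healing and has not been compared to results in actual patients". Section 1.1 says that "a Graphical User Interface (GUI) is being developed to allow the surgeon to remove tissue in a virtual environment" and that "an additional GUI will be developed to simulate changes that occur during treatment (eg, radiation therapy) and healing". It gives no date for completing either.

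**The reviewers.** Section 6.8 has two surgeons, from outside both the patient's care and the study, grade cosmesis on a 4-point scale. Section 4.1.1.2 lists as a secondary variable the "judgment of independent reviewers regarding the correlation of the cosmesis score to the multiscale prediction model". The footnote to the cosmesis-judging row in section 6.8.1 describes that activity as "Independent assessment of cosmesis using the Harvard/NSABP/RTOG cosmesis criteria and comparison to multiscale model".

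**The concern.** A test of predictive validity needs a fixed order: the prediction is recorded first, and the outcome is seen afterwards. The protocol describes a model whose healing component was still to come and a pass mark that scores that component. It does not state the order. If anyone building the model sees a subject's post-operative contour or ultrasound before her prediction is final, the score measures fit to known cases. A pass at 60% would then say little about the next patient, although the rationale in section 1.2 is to inform future patients before surgery.

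The second matter is smaller. Neighbouring grades on the cosmesis scale are separated by words such as slight and obvious, so they leave room for judgment. A grader who has the predicted shape in view, or who is also asked how well grade and prediction match, can drift towards the prediction. The likely direction is a better apparent match.

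**Working it through.** **1. The plan's own figure.** The only sample-size figure is enrolment of up to 15 to obtain 12 evaluable subjects (sections 4.1.2 and 7.1.1). With up to 3 replacements, 12 + 3 = 15, so it reproduces. It neither supports nor weakens this point.

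**2. Is a lock stated anywhere?**

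| Question | What the protocol gives |
|---|---|
| Is the model version fixed before the first subject? | Not stated. Section 1.1 uses the present progressive and the future tense, undated |
| Which data feed the prediction? | Pre-operative MRI and mammogram are required (4.1.4.1), and section 1.2 speaks of pre-operative imaging with virtual surgery; no rule limits the inputs to these |
| Is the prediction recorded before post-operative images are seen? | Not stated |
| Are development and test cases separate? | Not stated |
| Are graders blind to the prediction? | Not stated. Section 6.8 requires independence from care and study, which is a different safeguard |
| Are grades locked before the comparison? | Not stated. The 6.8.1 footnote puts both in one activity |

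**3. Which gap reaches which endpoint?** Section 4.1.1.1 defines the primary variables as camera contour and ultrasound dimensions, with their predicted counterparts. The quantitative score in section 7.1.3 uses lumpectomy dimensions, healing and contour. The model gap therefore reaches the 60% criterion and the reviewer gap does not. Section 7.1.3 lists only a summary of the cosmesis grades at weeks 10 and 26 and no reviewer judgment of the match, so it should be reconciled with section 4.1.1.2 and the 6.8.1 footnote.

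**4. Hypothetical illustration of tuning.** Three assumptions, none of them in the protocol: 60% is read as a correlation of 0.60; tuning acts like least squares with k free parameters on the same n subjects; and the model has no true predictive value. Then

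R² ~ Beta(k/2, (n − 1 − k)/2), with mean k/(n − 1), and P(R ≥ 0.60) = P(R² ≥ 0.36).

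Hand check for n = 12, k = 2: Beta(1, 4.5) gives (1 − 0.36)^4.5 = 0.64^4.5 = 0.134.

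| Tuned parameters k | Mean R², n = 12 (k/11) | P(R ≥ 0.60), n = 12 | P(R ≥ 0.60), n = 15 |
|---|---|---|---|
| 1 | 0.091 | 3.9% | 1.8% |
| 2 | 0.182 | 13.4% | 6.9% |
| 3 | 0.273 | 28.7% | 16.3% |
| 4 | 0.364 | 47.4% | 30.1% |
| 5 | 0.455 | 65.8% | 46.3% |

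For a prediction frozen beforehand, T = r·√[(n − 2)/(1 − r²)]. At n = 12, T = 0.6·√(10/0.64) = 2.37 on 10 degrees of freedom, one-sided probability 2.0%. At n = 15, T = 0.6·√(13/0.64) = 2.70 on 13 degrees of freedom, 0.9%.

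**The case against.** **The model may have been finished in time.** The future-tense sentence in section 1.1 concerns an interface and carries no date. Sections 2.1, 2.2.1 and 3 treat the model as an existing comparator. Section 1.2 describes prediction from pre-operative imaging, and section 3 says the data will be a basis for testing. A reader might infer that the model is built during the study and tuned on these 12 subjects. The documents do not support that: no passage describes fitting to outcomes, and development could be complete before the first patient. What stands is narrower. The component was unfinished at the time of writing, and no lock is stated.

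**The reviewers cannot move the primary result.** A reader might also infer that unblinded graders could help the study reach 60%. They cannot, because that score uses camera and ultrasound measures. Two qualitative items in section 7.1.3 refer to cosmetic outcome, but they carry no threshold. The graders are also outside the care and the study, which is a real but partial safeguard. That the same two surgeons both grade and compare comes from reading sections 4.1.1.2, 6.8 and 6.8.1 together; the footnote gives neither the person nor the order.

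**The illustration is not this model.** Section 1.1 describes a patient-specific mechanical model, not a regression. The protocol gives no parameter count, and it calls the 60% agreement in one place and accuracy in another, though it also speaks of correlation. This objection is right, and the figures show only how the risk grows with tuning.

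**It is a small pilot, and the details could sit in an analysis plan.** A pilot may develop a model, but this one states a validity test with a pass mark. When predictions are made and what graders see are rules of conduct that must be settled before data collection.

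**Conclusion.** The point holds as an omission in the design. The protocol claims a test of prediction for a model whose healing part was still to be developed, and it does not require each prediction to be fixed before the subject's post-operative images are seen. A pass at 60% could therefore not be told apart from tuning. It is not shown that tuning was planned or took place.

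The reviewer matter also holds, for a secondary variable only: grading and comparison with the model are joined without blinding to the prediction, which can bias the match upward.

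The protocol does not allow the size to be computed. The range of about 4% to 66% for 1 to 5 tuned parameters at n = 12, against about 2% when frozen, depends entirely on the three assumptions above and should not be read as this study's error rate. The change is worth making because it protects the stated purpose at little cost.

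**What to change.** 1. **Section 4.1.1:** state that each subject's prediction is generated with a fixed, identified model version from pre-operative imaging and operative data, and is date-stamped before her post-operative images are released to the modelling team. Any later re-tuned version is reported as exploratory.
2. **Sections 4.1.1.2 and 6.8, with the 6.8.1 footnote:** state that the two surgeons lock their grades without access to model output, and that the comparison with the model is computed from the locked grades and not judged by the graders. Bring section 7.1.3 into line, so that all places name the same secondary outcome.

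**Cost:** wording and control of file dates and access; no extra visits or staff. If the model was complete before the first subject, the first change only records that fact. The downside is that improvements made to the model during the study cannot count towards the primary result.

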#### 4.1.2 Number of subjects

Up to 15 de novo breast cancer subjects will be enrolled in order to allow for early drop-outs resulting in 12 evaluable cases.

#### 4.1.3 Study duration

The study will begin at the time of breast cancer surgery evaluation and subjects will be enrolled for six months post-surgery.

#### 4.1.4 Study population

Patients with breast cancer who are having BCT and who satisfy the following criteria will be considered for participation in this study.

##### 4.1.4.1 Inclusion criteria

1. Adult females  $\geq$  age 30 years
2. Have early stage (Stage I, II), non-metastatic breast cancer
3. Planned to receive BCT
4. Have received a pre-operative mammogram within 30 days of surgery
5. Have received pre-operative magnetic resonance imaging (MRI) within 30 days of surgery
6. Planned to receive post-surgery radiotherapy by whole breast radiotherapy
7. Signed informed consent form prior to any research assessment

##### 4.1.4.2 Exclusion criteria

1. Adult females younger than 30 years of age
2. Previous breast cancer
3. Neo-adjuvant therapy for breast cancer
4. Pregnant or nursing females
5. Participation in a study of investigational drug in the previous 30 days or 5 half-lives of the investigational drug

## 5 Treatment procedures

Standard of care for early stage breast cancer is breast conserving therapy at this center.

### 5.1 Other concomitant standard of care treatment

- Radiation therapy to the whole breast
  - 45-50 Gy delivered over 25-28 fractions with a boost to the tumor bed of 10-16 Gy delivered over 5-8 fractions

## 6 Study procedures

### 6.1 Consent process

After approval by The Methodist Hospital Research Institute's Institutional Review Board, the Principal Investigator, or a designated member of her study team, will approach potential subjects prior to surgery regarding participation in the study. The study will be described by explaining the purpose of the study, the methods and objectives and the potential risks associated with the study. An informed consent form (ICF) will be provided, patients will be given time to read the ICF and will be allowed to ask questions about the study. They will be informed that their participation is voluntary and that choosing not to be involved will not influence their care at The Methodist Hospital. They will be informed that they may choose to withdraw from the study at anytime for any reason. Subjects will be given an original informed consent form to keep. The informed consent process will be documented in the patient's chart.

Any new information about the study procedures that may be determined by the Principal Investigator to be necessary will be provided to the Institutional Review Board. Subjects will also

be provided this information through a revised informed consent form and will be given the opportunity to decide whether to continue in the study or not.

## **6.2 Assessment of eligibility**

Within 21 days prior to surgery, the subject may be approached regarding potential interest in study involvement. Their medical history will be reviewed to assess for eligibility. Prior to performing any research-related procedures, informed consent will be obtained. Subjects must meet all inclusion criteria and none of the exclusion criteria or enrollment will not be possible.

## **6.3 Enrollment**

Subjects who qualify for enrollment in this study, after signing informed consent, will be enrolled and proceed into the study at the time of consent. Imaging procedures and follow-up clinical appointments will be scheduled as described in Sections 6.4 through 6.7 below.

## **6.4 3-Dimensional Surface Imaging of the Breast**

A 3-dimensional 180° camera will be used to capture surface imaging prior to surgery and at three time-points after surgery (visits 2, 4 and 6). The surface imaging will provide measures of breast deformity.

## **6.5 Breast Ultrasound**

Breast ultrasound will be performed in the outpatient surgery clinic at visits 2, 3, 4, 5, and 6 using an office-application ultrasound system with a soft-tissue transducer, such as the SonoSite EDGE™ machine with HFL50x or HFL38x transducer.

## **6.6 Pain scale score**

Pain will be assessed prior to surgery and at each follow-up visit prior to the ultrasound procedure and following the ultrasound procedure.

## **6.7 Thermal Imaging of the Breast**

The healing process will be assessed by taking surface images with a thermal camera.

## **6.8 Judging**

Breast cosmesis will also be assessed using the 4-point Harvard/NSABP/RTOG cosmesis criteria scale (Appendix) and judged by two independent surgeons not involved in the care of the patient or the study. Judging will occur at baseline (after surgery) and at week 10 and week 26.

### 6.8.1 Sequence of events

| Month               |          |   | 1 |    |    |    | 3 | 6 |    |
|----------------------------|----------|---|----------|----|----|----|----------|----------|----|
| Week                |          |   | 1        | 3  | 6  | 10 | 12       | 24       | 26 |
| Visit day           | -21 to 0 |   | 1        | 2  | 3  |    | 4        | 5        |    |
| Visit window (days) | -21      |   | 0        | ±7 | ±7 |    | ±7       | ±7       |    |
| Visit number        | 1        |   | 2        | 3  | 4  |    | 5        | 6        |    |
| Parameter           |          |   |          |    |    |    |          |          |    |
| Informed consent           | X        |   |          |    |    |    |          |          |    |
| 3-D SI*                    | X        |   | X        |    | X  |    |          | X        |    |
| Surgery                    |          | X |          |    |    |    |          |          |    |
| Thermal image              |          |   | X        | X  | X  |    | X        | X        |    |
| Ultrasound†                |          |   | X        | X  | X  |    | X        | X        |    |
| Radiation therapy          |          |   | X        | X  | X  |    |          |          |    |
| Pain scale score‡          | X        |   | XX       | XX | XX |    | XX       | XX       |    |
| Cosmesis judging§          |          |   | X        |    |    | X  |          |          | X  |

\*3-dimensional 180° camera surface imaging

†Breast ultrasound of the tumor / lumpectomy area

‡Performed pre and post ultrasound

§Independent assessment of cosmesis using the Harvard/NSABP/RTOG cosmesis criteria and comparison to multiscale model

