**Figure 1. Study design.**

#### 4.1.1 Study endpoints

The primary endpoint of this study is the comparability of the surgical/healing outcome of the lumpectomy and breast surface contour to the predicted changes from the multiscale model. A mean combined score  $\geq 60\%$  agreement will be considered acceptable in this pilot project.

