### 7.1.3 Evaluation criteria:

- The primary outcome measure will be
- Qualitative:
  - confirmation that relative size of the lumpectomy to the breast, tissue composition ratio of fat versus glandular, and location of the tumor will provide a qualitative grading of the potential cosmetic outcome.
  - correlation of the wound edge shape to mechanical stress
  - correlation of volume loss due to healing to cosmesis outcome.
- Quantitative: a combined score of the correlation between three measured processes (lumpectomy dimensions, lumpectomy healing process, surface contour changes) and the predicted outcomes from the multiscale model measured/assessed at weeks 10 and 26 postsurgery with a mean accuracy rate of  $\geq 60\%$ .
- Secondary outcome measures will include postsurgery:
  - the proportion of subjects experiencing pain  $\geq 8$  on more than one measurement post operatively and the relationship of pain to the accuracy of the multiscale model
  - the proportion of subjects experiencing increased pain ( $\geq 3$  unit increase) pre to post ultrasound at each visit to determine the possible invasiveness of these multiple post-surgery ultrasounds
  - detection of changes in the thermal image of the breast tissue related to inflammation and healing
  - the summary of the independent judgment (Harvard/NSABP/RTOG scale score) of cosmesis taken at weeks 10 and 26

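### The primary score is set at weeks 10 and 26, but the images come from ±7-day visits that never reach those days, so a timing gap can count as model error

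*Protocol*

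**What the plan says.** All references are to the Protocol.

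- **What is scored.** Section 7.1.3 defines the quantitative primary outcome as "a combined score of the correlation between three measured processes (lumpectomy dimensions, lumpectomy healing process, surface contour changes", set against "the predicted outcomes from the multiscale model measured/assessed at weeks 10 and 26 postsurgery". The acceptance level there is a mean accuracy of at least 60%. Section 4.1.1 gives the same 60% level for a mean combined score: "agreement will be considered acceptable in this pilot project".
- **What is measured.** Section 4.1.1.1 names the measured inputs: "surface contour captured by the 3-dimensional 180° camera, lumpectomy dimensions captured by ultrasound".
- **When it is measured.** Section 6.4 places 3-D imaging before surgery and at "three time-points after surgery (visits 2, 4 and 6", which the schedule puts at weeks 1, 6 and 24. Section 6.5 says "Breast ultrasound will be performed in the outpatient surgery clinic at visits 2, 3, 4, 5, and 6", which are weeks 1, 3, 6, 12 and 24.
- **Windows.** The row "Visit window (days" in 6.8.1 gives 0 for visit 2 and ±7 for visits 3 to 6. The week 10 and week 26 columns have no visit number and no window; cosmesis judging is the only item marked there.
- **What the model does.** Section 1.1 says that "an additional GUI will be developed to simulate changes that occur during treatment (eg, radiation therapy) and healing", so the prediction under test changes with time since surgery.

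**The concern.** A model of healing is tested by comparing its output with a measurement. If the output is for one day and the measurement is from another, part of the difference between them is healing that happened in between. A perfect model would show that difference too.

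Section 7.1.3 gives one time reference for the primary score, two fixed weeks, and none of the imaging visits falls on them. The visit windows then make the gap vary from woman to woman. The result is judged against a fixed 60% level in about 12 evaluable women, so lost agreement that has nothing to do with the model could affect whether the model is called acceptable.

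**Working it through.** **Inputs.** Visit weeks and windows are from 6.8.1, imaging visits from 6.4 and 6.5, and scoring weeks from 7.1.3. Week w is counted as day 7w after surgery. The plan states no figure on timing error to reproduce. Its one sample-size figure, 15 enrolled less 3 replaceable withdrawals = 12 evaluable, is not affected.

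**Step 1: days each visit can occupy** (7w ± window).

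| Visit | Nominal day | Permitted days | Ultrasound | 3-D image | 7 days as share of elapsed time |
|---|---|---|---|---|---|
| 4 (week 6) | 42 | 35–49 | yes | yes | 7/42 = 17% |
| 5 (week 12) | 84 | 77–91 | yes | no | 7/84 = 8% |
| 6 (week 24) | 168 | 161–175 | yes | yes | 7/168 = 4% |

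**Step 2: gap to the scoring days** (10 × 7 = 70 and 26 × 7 = 182).

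| Score component | Nearest visit | Nominal gap | Range within window |
|---|---|---|---|
| Ultrasound, week 10 | 5 | 84 − 70 = 14 days | 7–21 days |
| Contour, week 10 | 4 | 70 − 42 = 28 days | 21–35 days |
| Ultrasound and contour, week 26 | 6 | 182 − 168 = 14 days | 7–21 days |

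Even perfectly timed visits leave a gap of 14 or 28 days. The window shifts it by up to 7 days either way, so two women at the same visit can differ by up to 14 days.

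**Step 3: how the gap could reach the score.** Section 4.1.1 speaks of agreement and 7.1.3 of correlation. If the score measures agreement in size, both the fixed gap and its variation can lower it. If it is a correlation across women, a gap common to all may largely cancel and the variation from the windows is what matters. The formula is not given, so the effect on the score cannot be computed.

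**Step 4: illustration under an assumption.** The protocol gives no healing rate. Suppose the cavity shrinks exponentially with half-life H days, so the fraction remaining on day t is 2^(−t/H). A visit 7 days early changes the remaining volume by 2^(7/H) − 1; a visit 7 days late lowers it by 1 − 2^(−7/H). Multiplying the early change by the fraction remaining gives points of the original cavity volume.

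| H (days) | 7 days early | 7 days late | Left at day 84 | Early visit 5, points | Left at day 168 | Early visit 6, points |
|---|---|---|---|---|---|---|
| 14 | +41.4% | −29.3% | 1.6% | 0.6 | 0.02% | 0.01 |
| 28 | +18.9% | −15.9% | 12.5% | 2.4 | 1.6% | 0.3 |
| 56 | +9.1% | −8.3% | 35.4% | 3.2 | 12.5% | 1.1 |
| 112 | +4.4% | −4.2% | 59.5% | 2.6 | 35.4% | 1.6 |

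The nominal 14-day gap lowers the remaining volume by 1 − 2^(−14/H), which is 50%, 29%, 16% or 8% for the four half-lives. At visit 6 the largest of these in points of original volume is 35.4 × 8.3% = 2.9 (H = 112).

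The relative changes can look large, but they apply to a small remainder. This concerns cavity volume only; nothing in the document allows the same calculation for contour.

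**The case against.** The strongest reply is that no section says for which day the model is run. The timing phrase in 7.1.3 can be read as saying when the assessment is made, not what time is fed into the simulation. A footnote in 6.8.1 supports this: it attaches a comparison with the model to the cosmesis judging, which takes place at weeks 10 and 26. A time-dependent simulation could be evaluated at the actual imaging day without breaking any stated rule. This stands, and it is why the point is that timing *can* be counted as model error, not that it will be. It does not remove the point: under that reading the section still does not say which image is used. At week 10, visit 5 has normally not yet taken place, so the ultrasound might be visit 4's, 21–35 days before day 70.

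A second reply is that handling of visit windows belongs in a statistical analysis plan, which is not at hand. That is fair for windows alone. But section 7 is the protocol's own analysis plan, and 7.1.3 itself fixes the scoring weeks; the objection here is to that stated rule.

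A reader might go further and infer that all visits are loosely timed, or that women scanned anywhere in the week 3 window are compared with one predicted contour. The documents do not support this: visit 2 has a window of 0, and visit 3 has no 3-D image and is not a scoring time. A reader might also infer bias, with slow healers attending late. No section links attendance to healing, so this remains conjecture.

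**Conclusion.** The point holds in limited form. The date arithmetic is firm: no permitted imaging visit reaches day 70 or day 182, the gap is 7–21 days (21–35 for contour at week 10), and it can vary by up to 14 days between women at one visit. Read as written, the rule in 7.1.3 lets that gap be counted against the model.

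The effect on the 60% criterion is unknown. The illustrative percentages rest wholly on an assumed exponential healing rate, and even under it the effect at visit 6 is probably small. The tempting stronger conclusion, that ordinary scheduling noise is scored as model error and decides pass or fail, is not established: the protocol neither says that predictions are run at nominal weeks nor gives a score formula. For a 12-woman observational pilot, this is an inexpensive improvement to the stated rule and does not put the study in doubt.

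**What to change.** In 7.1.3, make two changes:

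1. Name the imaging visits that feed the primary score, separately for ultrasound and 3-D contour, so that the scoring times and the schedule in 6.4, 6.5 and 6.8.1 agree.
2. State that each predicted contour and lumpectomy dimension is output for the actual number of days from surgery to the image or scan it is compared with. Keep the nominal week only as a label in tables.

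The first change resolves the mismatch between weeks and visits. The second removes the remaining ±7-day difference.

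This is a free improvement costing about two sentences. It needs no added visit, procedure or subject. The pain form in Appendix 16.2, completed before and after each ultrasound, already carries the date and visit, and every post-surgery 3-D image is scheduled at a visit that also has an ultrasound. The one condition is that the healing simulation can be output for any chosen day, which its described purpose in section 1.1 implies but does not state.
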